#### Secondary outcomes

The main secondary outcomes at the community level include:
The proportion of these children under 5 years of age, who received MRDT, whose caregivers requested the MRDTThe proportion of these children ages 5 years and above and adults, who received MRDT, who requested or whose caregivers requested the MRDTThe proportion of children under 5 years of age with fever or malaria-like illness, in the 2 weeks preceding a population-based household survey, whose caregivers sought care with a provider, those that sought care the same or next day and among those for whom care was sought, the type of provider with whom care was soughtThe proportion of these children under 5 years of age who took any anti-malarial drug and who took ACTs.The proportion of children ages 5 years and above and adults (excluding pregnant women) with fever or malaria-like illness, in the 2 weeks preceding a population-based household survey, who sought care with a provider, those who sought care the same or next day and among those who sought care, the type of provider with whom care was soughtThe proportion of these children and adults who took any anti-malarial drug and who took ACTs.The proportion of respondent female heads of households (female primary care givers) with good knowledge and opinion about malaria and malaria diagnosis.

The secondary outcomes at the provider level include:
The number of patients with suspected malaria visiting the public primary health facilities (monthly) as identified in the patients’ registerThe proportion of providers with good knowledge and opinion and good health communication about malaria and malaria diagnosis.

Cost outcomes include the total cost of the social group and social group/provider interventions, average cost per provider who participated in the provider training and average cost per social group member who participated in the social group sensitization/education.

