#### Review of the patient register and personal medical records

Patient registers are routinely kept by public primary health facilities. The following relevant data are contained in the registers: the patient’s biodata (name, age, sex, address, etc.), date, symptoms, type of test performed, test result and type of drug given. The participating PMVs will be asked to keep similar records. The registers will be used by the research team for monitoring, supportive supervision and evaluation. The investigators will review the patient registers for 9 months pre-intervention and 9 months post end-of-intervention records. The document review will provide data for evaluating the effect of the interventions on the number of patients with suspected malaria visiting the public primary health centres.

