#### Sample size

After comparing the required sample size for each of the primary objectives, the largest sample size will be used. This is based on the primary objective to evaluate the effectiveness of the social group/provider intervention compared to the social group intervention in increasing the demand for MRDT in the communities. The sample size is estimated using the methods recommended for a stratified, cluster-randomized trial [39, 40] and will be based on the primary outcome of the proportion of children under 5 years of age with fever or malaria-like illness, in the 2 weeks preceding a population-based household survey, who received MRDT. A plausible estimate of the primary outcome of 11% in the control arm will be used, based on the reported value for the south-east zone (that includes Ebonyi state) in the NMIS 2015 [15].

Assuming a coefficient of variation between clusters within strata of 0.16, a sample size per cluster of 40 eligible children under 5 years of age and 80% power at 5% probability of type I error, the trial will require 6 clusters per arm to detect a difference of 20% in the primary outcome between the control arm and the social group arm (an increase from 11% to 31%) and a difference of 20% between the social group arm and the social group/provider arm (an increase from 31% to 51%). A sample size per cluster (cluster size) of 40 subjects with 6 clusters per arm gives a total cluster number of 18, with 240 subjects per arm and a total sample size of 720 subjects. The sample size per cluster (of 40) will be increased by 20% (to 50) to compensate for any probable invalid records and other field eventualities. This gives a final cluster size of 50 subjects with 300 subjects per arm and a total sample size of 900 subjects.

The same sample size will be used to assess the co-primary outcome of the proportion of children ages 5 years and above and adults (excluding pregnant women) with fever or malaria-like illness, in the 2 weeks preceding a population-based household survey, who received MRDT. An equal number of clusters (*n* = 6) will be allocated to each arm and to each stratum and, despite variations in population size in the clusters, an equal fixed sample size (*n* = 50 for each target population) per cluster will be used to optimize statistical efficiency [39, 40].

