#### Data analysis

Data will be double-entered using Microsoft Excel 2007 (Microsoft Inc., Redmond, WA, USA) and analysed using Stata version 15 (Stata Corp, College Station, TX, USA). Since the number of subjects/household members on whom data will be collected is expected to vary across clusters (due to the method employed for the household survey), the “sample” command will be used to randomly select an equal number of subjects across clusters for analysis. All analyses will be on an intention-to-treat basis.

The effect of the interventions on the primary outcome will be analysed using cluster-level methods for stratified, cluster-randomized trials with a small number of clusters per treatment arm [39, 40]. Point estimates of the intervention effects (risk difference) in each intervention arm compared to control and in both of the intervention arms compared to each other will be computed from the unweighted mean of cluster-level summaries (proportions) of the outcome measures in each study arm. But since the cluster size (sample size across clusters) is constant, this point estimate will be identical to that obtained from the weighted average of individual values [39, 40]. Also, since the number of clusters across strata is constant, the estimated risk difference will be identical to the weighted average of stratum-specific risk difference.

An overall test of the null hypothesis of no difference between any of the study arms will be conducted in a two-way analysis of variance (ANOVA) of the cluster-level proportion on stratum and treatment arm. This overall test is to guide the interpretation of any subsequent significant findings in pair-wise comparisons. If the distribution of the cluster summaries in each study arm is markedly skewed, logarithmic transformation may be considered before analysis. Before conducting pair-wise significance testing and computing a confidence interval, an estimate of the within-stratum between-cluster variance will be obtained as the residual mean square from two-way ANOVA of the cluster-level proportions on stratum and treatment arm, including interaction terms. The within-stratum between-cluster variance will then be used in a stratified *t* test to test the null hypotheses of no difference in the primary outcome between each intervention arm and the control and between the two intervention arms. It will also be used in computing the corresponding 95% confidence interval of each risk difference.

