Adjusted analysis based on cluster summaries will be done in a two-staged procedure. In the first stage, the covariate-adjusted residual will be obtained for each cluster using standard multiple linear regression analysis, incorporating the stratum (as a fixed effect) and all baseline cluster-level covariates of interest but excluding the intervention effect. The potential baseline covariates of interest will include cluster-level summaries of the primary outcome measure, mean scores for respondents’ knowledge and opinions (about malaria and malaria diagnosis) and other baseline variables found to differ between the study arms and which can be determinants of a particular outcome. Only cluster-level summaries of baseline covariates will be used in the adjusted analysis because baseline and follow-up data will be on different individuals, as the study employed a repeated cross-sectional design [39, 40]. The difference-residual for each cluster will be obtained as the difference between the observed outcome in each cluster and the predicted outcome in the absence of an intervention effect. The covariate-adjusted residuals will replace the cluster-level proportions in the second stage in estimating the intervention effects, which are thus adjusted for the covariates in the first stage.

The same cluster-level methods will be used to evaluate the effect of the interventions on the secondary outcomes. Comparative analysis of baseline data will be used to assess the balance between the treatment arms and potential baseline variables that will be reported include the cluster-level and individual-level summaries of the primary and secondary outcome measures, the age and sex of individual subjects, the age of the respondent female head of household, educational level, occupation, level of knowledge and opinions about malaria and malaria diagnosis and average knowledge and opinion score. Summary statistics of baseline data will be used to assess the level of demand for MRDT, care-seeking practices and pattern of anti-malarial drug use among community members with fever or malaria-like illness; the level of knowledge and opinions of the female heads of households about malaria and malaria diagnosis and the level of knowledge and opinions of healthcare providers about malaria and malaria diagnosis.

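### Facility attendance is a raw count, but the plan does not commit to adjusting for each cluster's own pre-intervention attendance, which is already being collected

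*Protocol article*

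**What the plan says.** The Secondary outcomes section of the protocol article lists, at provider level, "The number of patients with suspected malaria visiting the public primary health facilities (monthly", taken from the patients' register. No denominator is given.

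The section on review of the patient register says the investigators will "review the patient registers for 9 months pre-intervention and 9 months post end-of-intervention records". It gives the purpose as follows: "The document review will provide data for evaluating the effect of the interventions on the number of patients with suspected malaria". It does not say how the pre-intervention half enters the comparison.

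The Data analysis section describes two analyses for the primary outcome:

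- **Unadjusted.** The effect is a risk difference "computed from the unweighted mean of cluster-level summaries (proportions) of the outcome measures in each study arm", tested with a stratified t test on the within-stratum between-cluster variance. A log transformation is optional if the summaries are markedly skewed.
- **Adjusted.** A two-stage residual analysis uses baseline cluster-level covariates. The potential covariates "will include cluster-level summaries of the primary outcome measure", mean knowledge and opinion scores, and other baseline variables on which the arms are found to differ and which could determine the outcome.

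The section then adds: "The same cluster-level methods will be used to evaluate the effect of the interventions on the secondary outcomes". Baseline summaries of the secondary outcomes are mentioned separately, for assessing balance between arms.

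**The concern.** The primary-outcome methods rest on a feature that attendance lacks. For the survey outcomes, an equal number of subjects is drawn per cluster and the summary is a proportion, so cluster size drops out. A register count has no such equalisation. Under Methods/design and Participants, clusters have a minimum population and at least one facility, and facilities have a minimum daily number of fever patients; none has a maximum. The Sample size section fixes equal samples "despite variations in population size in the clusters". Differences in facility and catchment size therefore go straight into the between-cluster error term. A log transformation changes the scale but does not remove them.

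The natural remedy is each cluster's own earlier count. Its use under the adjusted analysis depends on an observed difference between arms. That is a weak criterion with six clusters per arm: a baseline that strongly predicts the outcome improves precision even when the arms happen to be balanced on it. What is at stake is the precision of one secondary comparison, and an avoidable data-dependent choice in its analysis.

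**Working it through.** **1. The plan's own figure.** The article gives no power or precision for attendance. Its only related figure is six clusters per arm for the primary outcome (Sample size: 31% versus 51%, coefficient of variation k = 0.16, m = 40 per cluster, 80% power, 5% type I error, taken as two-sided).

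Core term = (1.96 + 0.842)² × [p0(1−p0)/m + p1(1−p1)/m + k²(p0² + p1²)] / (p0 − p1)²

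= 7.849 × [0.00535 + 0.00625 + 0.00912] / 0.04 = 4.06

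The usual small-sample addition of 1 gives 5.06, rounded up to 6, so the stated number reproduces. (An addition of 2 gives 6.06.) The k of 0.16 describes a proportion and says nothing about variation in counts.

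**2. The two register windows.** Nine months before a three-month intervention and nine months after it start 9 + 3 = 12 months apart. If they adjoin the intervention, they cover the same calendar months, so the earlier count is already matched for season.

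**3. Inputs for attendance.** From the plan: 6 clusters per arm, and an error term from the two-way analysis of variance with interaction, hence 18 − 9 = 9 degrees of freedom. Assumed, because the documents give neither: between-cluster coefficient of variation (CV) and pre-post correlation r of the log counts.

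**4. Formulas.**

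- Log-scale SD: s = √ln(1 + CV²)
- Unadjusted 95% CI factor: exp(t₉ × s × √(2/6)), with t₉ = 2.262
- With own baseline: replace s by s√(1 − r²)

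The lower and upper limits are the estimated ratio divided and multiplied by this factor.

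Example, CV 0.5: s = 0.472. Unadjusted: exp(2.262 × 0.472 × 0.577) = 1.85. With r = 0.9: s√(1 − 0.81) = 0.206, factor 1.31.

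**5. Results (95% CI factor).**

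| CV | No baseline | r = 0.5 | r = 0.7 | r = 0.9 |
|---|---|---|---|---|
| 0.3 | 1.47 | 1.39 | 1.32 | 1.18 |
| 0.5 | 1.85 | 1.71 | 1.55 | 1.31 |
| 0.7 | 2.28 | 2.04 | 1.80 | 1.43 |

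The adjusted columns keep 9 degrees of freedom. Charging one for the covariate (t₈ = 2.306) changes little: 1.31 becomes 1.32, and 1.80 becomes 1.82.

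**6. The same in terms of power.** Smallest ratio detectable with 80% power (noncentral t; 9 degrees of freedom unadjusted, 8 adjusted):

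| CV | No baseline | r = 0.5 | r = 0.8 | r = 0.9 |
|---|---|---|---|---|
| 0.2 | 1.43 | 1.37 | 1.25 | 1.17 |
| 0.5 | 2.36 | 2.13 | 1.69 | 1.46 |
| 0.7 | 3.15 | 2.75 | 2.01 | 1.66 |

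At CV 0.5, power for a 50% rise is 26% without the baseline, 59% with r = 0.8 and 85% with r = 0.9.

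**The case against.** The strongest reply is that the plan does not ignore baseline. The sentence on secondary outcomes follows the description of the adjusted analysis, so it carries over both analyses. For the primary outcome the first covariate named is that outcome's own baseline, and one could read the carried-over method as using baseline attendance here. If facility size is unbalanced by chance, earlier attendance would differ between arms, would plainly be a determinant, and would qualify. The register section ties the records from both periods to evaluating the effect. The outcome is secondary, and a fuller plan that is not shown may settle the model.

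Much of this stands. A reader might infer that the plan offers only an unadjusted test of post-intervention counts; the text does not support that. The imbalance rule also covers part of the risk of chance imbalance, and randomisation within strata keeps the unadjusted comparison unbiased.

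A reader might also infer that facility size must swamp any effect, or that no plausible change could be detected. That is not established either. The documents give no between-facility variation, pre-post correlation or expected change in attendance, and having no upper size limit does not prove wide variation. At a CV of 0.2 a ratio of 1.43 is detectable without any baseline.

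One point remains unanswered. The article names the primary outcome's baseline, not that of whichever outcome is being analysed, and nothing commits to using earlier attendance when the arms look balanced.

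**Conclusion.** The point holds as one of precision and prespecification on a single secondary outcome. Methods built for proportions are applied to a count that carries facility and catchment size, and use of the best available covariate is left to an observed difference between arms. The unadjusted estimate is unbiased but may be imprecise. Over assumed CVs of 0.3 to 0.7 the confidence factor is 1.47 to 2.28 without the baseline, against 1.18 to 1.80 with it at correlations of 0.7 to 0.9. The two ranges overlap because they span different assumptions; at any one CV the adjusted factor is the smaller. If the correlation is near 0.5 there is little to gain: at CV 0.5 the detectable ratio moves only from 2.36 to 2.13. All these sizes rest on assumed values. The primary and co-primary analyses are unaffected.

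**What to change.** In the Data analysis section, give attendance its own sentence. The main analysis takes log(post-intervention count) per cluster as the outcome, with log(pre-intervention count) as a covariate whatever the observed balance, plus stratum and arm, and reports a ratio of attendance with its 95% confidence interval. State that both counts come from the two nine-month register windows already planned.

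The cost is analysis wording only, with no new data. It uses one error degree of freedom, and the effect is expressed as a ratio instead of a difference.

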## Discussion

This study, in investigating whether the social group and social group/provider interventions will increase the demand for malaria rapid diagnostic test (MRDT) among community members, will use a cluster-randomized design due to its pragmatic nature, as it is occurring in natural settings, and to minimize contamination as the interventions are behavioural and are delivered to groups of individuals. The research team is collaborating with the Ebonyi State Malaria Eradication Programme (SMEP) to enhance successful implementation of the study. Continuous collaboration with the Ebonyi SMEP, and by extension the National Malaria Elimination Programme (NMEP), will provide an opportunity for the study findings to contribute to both state and national policies that will enhance the realisation of universal parasitological diagnostic testing in suspected cases of malaria. A potential limitation of this study is due to the fact that the study will, in most part, involve interviewing respondents about past behaviour and will thus be subject to recall bias. However, as the time period is short (2 weeks) the bias will be minimal. Any significant amendments to the trial protocol after protocol publication will be reported to the research and ethics committees and the registry body. Study results will be reported at local, national and international levels including in peer-reviewed journals and at national and international conferences.

### Trial status

The trial is ongoing. Recruitment of participants began on 27 August 2018 and is expected to end by 29 June 2019. Protocol version: original, dated 24 August 2018.

## Data Availability

The datasets used and/or analysed during the current study will be available from the corresponding author on reasonable request.

## Abbreviations

ACTs: Artemisinin-based combination therapies
ANOVA: Analysis of variance
FGD: Focus group discussion
MRDT: Malaria rapid diagnostic test
NMIS: Nigeria Malaria Indicator Survey
PMVs: Patent medicine vendors
WHO: World Health Organization
